##### 8.1.1.1. OS

The hazard rate for the experimental versus the retrospective control group and its two-sided 80 and 95% CIs will be estimated using a Cox proportional hazards model. We will adjust for confounding using propensity scores.. Omission of 4 fractions as non-inferior to 10 fractions of radiotherapy if the higher 90% CI of the hazard ratio (HR) of 4 fractions versus 10 fractions was not above 1.4.

Only when non-inferiority has been demonstrated, we will test for superiority of the experimental treatment in a hierarchical fashion, using Kaplan-Meier method and two-sided log-rank test at a significance level  $\alpha = 10\%$  in ITT analysis.

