### 4.4 Sample size calculation

The sample size required to achieve a power of  $1-\beta = 0.80$  for the one-sided chi-square test at level  $\alpha = 0.05$  when the hazard ratio is actually 0.90, and a distribution of 40% in the intervention group and 60% in the control group, amounts to 165 subjects: 99 in the control group and 66 in the treatment group [30]. The non-inferiority ratio is 1.4. Unfortunately, there are no historical randomized placebo-controlled trials for arm 2 to use to formulate a margin, therefore we collect this data now as well for matched patients. This ratio is based on clinical judgment of the calculated survival fractions at the proposed non-inferiority margins and published survival data [21].

To clarify the meaning of this non-inferiority margin in practice, the non-inferiority margin specific survival fraction at median survival time could be calculated. This non-inferiority margin means in practice that at least 76% of the patients surviving at the median survival

time of the control group would have survived when treated with the experimental treatment. In other words, at least 38 percent of the patients in the intervention group reach the median survival time instead of 50 percent in the control group.

Expected event rate at the minimal follow-up time of 12 months is 0.7 based on the literature [21, 31]. However, a part of the study population may have a longer follow-up period of even up to 3.5 years. It is anticipated that the proportion of subjects observed with the event during the total study period is 0.8. These results assume that the hazard ratio is constant throughout the study and that Cox proportional hazards regression or the non-inferiority log rank test is used to analyze the data. To compensate for any drop-outs or slight deviation from the assumptions made, the total sample size should be 130 patients (10% added to the calculated sample size).

A point of discussion is that we anticipated that the hazard ratio is actually 0.90, however we can in fact not know the actual hazard ratio. It is justified to assume a hazard ratio below 1.0 when hypothesizing that the tumor will be treated slightly better by a higher dose per fraction.

**Table 1. Number of patients to include to achieve a power of 0.80 with a non-inferiority ratio of 1.4 at a decrease rate of 0.80 for different alfa-levels and actual hazard ratios.**

| Alfa/HR | 0.8 | 0.9 | 1.0 |

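### The overall survival analysis lists 80% and 95% intervals but decides non-inferiority on a 90% interval whose sidedness is not stated

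*Protocol*

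**What the plan says.** Section 4.4 of the Protocol sizes the trial "for the one-sided chi-square test at level" 0.05 with power 0.80, "when the hazard ratio is actually 0.90, and a distribution of 40% in the intervention group and 60% in the control group". It adds that "The non-inferiority ratio is 1.4" and that "the proportion of subjects observed with the event during the total study period is 0.8". The result "amounts to 165 subjects: 99 in the control group and 66 in the treatment group".

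Section 8.1.1.1 then specifies the analysis. For the hazard ratio of the experimental against the control group, "its two-sided 80 and 95% CIs will be estimated using a Cox proportional hazards model", with adjustment by propensity scores. The sentence that states the decision has no main verb. Its condition is met "if the higher 90% CI of the hazard ratio (HR) of 4 fractions versus 10 fractions was not above 1.4". It does not say whether the 90% refers to a two-sided interval or to a one-sided limit. Once non-inferiority is shown, the same section tests superiority with a two-sided log-rank test at 10%.

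No other section of the Protocol lists a two-sided 90% interval for the overall survival hazard ratio.

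**The concern.** Two adjacent statements about the primary analysis do not fit together. The intervals to be estimated are 80% and 95%, and the interval that decides the trial is 90%. An analyst who reconciles them from this paragraph alone can do so in two ways:

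- Take the rule as the upper limit of a two-sided 90% interval, and accept that the list of intervals is wrong.
- Take the rule as a one-sided 90% limit. This is the upper end of the two-sided 80% interval, which is on the list and has no other stated use.

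The first reading tests at one-sided 0.05 and the second at one-sided 0.10. This is the primary decision threshold of an open-label trial. Of its 99 controls, 83 come from a retrospective registry of recurrences between 2002 and 2022, so much of the control outcome may already be known. The choice between the readings should not be left until the hazard ratio has been seen.

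**Working it through.** **Inputs, all from section 4.4 unless noted.** One-sided alpha 0.05; power 0.80; assumed hazard ratio 0.90; margin 1.4; allocation 0.4 and 0.6; event proportion 0.8; 165 patients. The interval levels are from section 8.1.1.1.

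**Step 1: reproduce the planned size.** With the Schoenfeld formula for non-inferiority,

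events = (z(1−alpha) + z(power))² / [0.4 × 0.6 × (ln(0.90/1.4))²].

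Here z(0.95) = 1.6449, z(0.80) = 0.8416 and ln(0.90/1.4) = −0.4418, so

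events = (2.4865)² / (0.24 × 0.1952) = 131.96, that is 132;

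N = 131.96 / 0.8 = 164.95, that is 165.

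The stated 165 is therefore the size for one-sided 0.05. At one-sided 0.10 the same inputs give 96.22 events and 121 patients.

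**Step 2: match interval level to test level.** Requiring the upper limit of a two-sided interval of level 1 − 2a to be no higher than 1.4 is a one-sided test at level a. A two-sided 90% interval gives 0.05, which is the design level. A two-sided 80% interval gives 0.10. The factor of two follows from the levels alone and does not depend on the standard error.

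**Step 3: size of the difference.** With 132 events at 40:60,

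SE(log HR) = 1 / √(132 × 0.24) = 0.1777.

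The largest observed hazard ratio that passes is 1.4 × exp(−z × SE). Power at a true hazard ratio of 0.90 is Φ(0.4418/SE − z), where 0.4418/0.1777 = 2.487.

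| Reading of the 90% limit | z | One-sided level | Passes up to observed HR | Power at HR 0.90 |
|---|---|---|---|---|
| Upper limit of two-sided 90% interval | 1.6449 | 0.05 | 1.4 × exp(−0.2922) = 1.045 | Φ(0.842) = 80.0% |
| One-sided 90% limit (upper end of two-sided 80% interval) | 1.2816 | 0.10 | 1.4 × exp(−0.2277) = 1.115 | Φ(1.205) = 88.6% |

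The verdicts differ only when the observed hazard ratio lies between about 1.045 and 1.115. The chance of that is 88.6% − 80.0% = 8.6% at a true hazard ratio of 0.90, and 10% − 5% = 5% at a true hazard ratio of 1.4.

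**Step 4: where the 80% might come from.** Table 1 in section 4.4 gives 116 patients at alpha 0.10 and hazard ratio 0.9. This reproduces at 1:1 allocation: 92.37 events, and 92.37 / 0.8 = 115.46. Adding 10% gives 116 × 1.1 = 127.6. Section 4.4 still says that "the total sample size should be 130 patients (10% added to the calculated sample size"), and 127.6 is near that figure. The 80% interval may therefore be left over from a one-sided 0.10 design. This is an inference, because the Protocol does not state the alpha of the earlier randomized trial.

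**The case against.** The strongest reply is that the ordinary reading is already the right one. The higher limit of a 90% confidence interval normally means the upper end of a two-sided interval, which is one-sided 0.05. That agrees with section 4.4, where 165 reproduces only at that level. It also agrees with the superiority test in section 8.1.1.1, since a two-sided 10% test corresponds to a two-sided 90% interval. Only the 80 is out of line. This stands, and it decides which way the text should be corrected.

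A reader might infer more than the Protocol supports, in four ways:

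- *That the plan tests at twice its design level.* This needs the one-sided reading and also requires setting aside the explicit 0.05 in section 4.4. The listed 80% interval keeps that reading open but does not establish it.
- *That the deciding interval will not be computed.* The decision sentence itself calls for a 90% limit, so applying the rule means computing one. The fault is that the list of intervals omits the two-sided version.
- *That the 95% interval is a third candidate for the decision.* Nothing in section 8.1.1.1 sets it against the margin.
- *That the earlier trial was designed at one-sided 0.10.* The figure of 127.6 is suggestive, but it is not 130.

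It can also be said that section 8.1 allows minor revisions and requires a final statistical analysis plan before any formal analysis, so the correction can be made there. That is a route to the fix. It does not remove the mismatch from the Protocol as written.

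**Conclusion.** The point holds as an inconsistency in the primary decision rule: the intervals listed for the overall survival hazard ratio do not include the one that the design level requires, and the sidedness of the deciding limit is not stated. The consistent reading is the upper limit of a two-sided 90% interval. The other reading is less consistent but available, and it would double the one-sided error from 0.05 to 0.10.

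The practical effect is confined to observed hazard ratios of about 1.045 to 1.115. These limits assume 132 events, 40:60 allocation and an unweighted analysis. Section 8.1.1 specifies stabilized inverse probability weighting, which can change the standard error, so the limits and power figures are approximate. The link between interval level and test level is not affected. The sample size and the margin are not called into question by this point.

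**What to change.** In section 8.1.1.1, change the listed intervals to two-sided 90% and 95%. Rewrite the decision as a complete sentence: 4 fractions are non-inferior to 10 if the upper limit of the two-sided 90% confidence interval (one-sided alpha 0.05) of the propensity-weighted hazard ratio, 4 versus 10 fractions, is not above 1.4. State that the 95% interval is descriptive. Carry the same wording into the statistical analysis plan, and settle it before the arms are compared on survival.

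The cost is a rewording of two adjacent sentences. It adds no patients and changes neither the margin, the endpoint nor the planned 165.

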##### 8.1.1.2. PFS

The primary comparison of the time-to-event distributions between the two treatment arms will be done using the two-sided log-rank test at significance level  $\alpha = 5\%$  The hazard rates for the experimental versus the retrospective control group and its two-sided 95% CI will be

estimated using a Cox proportional hazards model. We will adjust for confounding using propensity scores.

### **8.1.2 Recurrence patterns**

Recurrence patterns will be compared between the arms using logistic regression, also adjusted for confounding using propensity scores. Recurrences are defined as “central” if more than 95% of the tumor recurrence resides within the prescription 95% isodose surface (D95) of the PTV; “in-field” if more than 80% of recurrent lesion is inside D95 of the PTV, and “marginal” if 20% to 80% of the lesion is inside D95 of the PTV. In all other cases, recurrences are defined as outside the radiation field (“ex-field”) according to the study of Lee et al. [44].

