### 2.2 Secondary Objective(s):

1. To compare progression free survival between the two treatment groups.
2. To describe health-related quality of life (HRQoL) in the experimental treatment group
3. To assess neurocognitive functions in a subgroup of the treatment group.
4. To describe toxicity in the experimental treatment group, and compare grade  $\geq 3$  toxicity in both groups.
5. To establish and compare recurrence patterns on MRI between the two treatment groups.

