#### 6.1.2 Secondary study parameters/endpoints

The key secondary endpoint is:

- Progression free survival (PFS) counted from the first date of re-irradiation until the date of MRI evidence of tumor recurrence or death due to any cause. Agreement of the tumor board or a consultant neuro-radiologist that imaging changes are in keeping with recurrence and not radionecrosis is necessary.

Other secondary endpoints include the following:

- Recurrence Patterns on MRI.
- Radiation toxicity graded by CTCAE v5.0
- Anti-edema therapy (including Dexamethasone and Bevacizumab use).
- Health Related Quality of Life (HRQoL) prospectively monitored by EQ-5D-5L, EORTC QLQ-C15-PAL and EORTC-QLQ-BN20+2 questionnaires. (only for the experimental arm 1, cannot be analyzed retrospectively in the control arm 2).

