### **8.1.4 Toxicity**

Toxicity will only be assessed in the experimental group. Analyses of radiotherapy toxicity will be performed in all patients who received at least one fraction. Acute events occurring from start of radiotherapy until 90 days and late events occurring from 91 days after end of radiotherapy will be presented. Further analyses of treatment toxicity will present the grade 3 to 5 acute or late side effect by treatment arm. The time to occurrence of any severe late side effects and separately radionecrosis (distinguishing symptomatic and asymptomatic) will be estimated by cumulative incidence. The time to severe late side effects will be calculated from the time of start of radiation treatment to the first evidence of any grade 3-5 late side effects. Patients alive without grade 3-5 late toxicity will be censored at the date of last

follow-up, patients who died without experiencing late grade 3-5 side effects will be assessed as competing risk at the time of death.

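### The logistic comparison of recurrence patterns is in effect restricted to patients who recur, so it cannot tell fewer in-field failures from more ex-field failures, and two of its classes overlap

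*Protocol*

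**What the plan says.** Secondary objective 5 (Protocol section 2.2) is a between-arm comparison: "To establish and compare recurrence patterns on MRI between the two treatment groups". Section 8.1.2 fixes the method: "Recurrence patterns will be compared between the arms using logistic regression, also adjusted for confounding using propensity scores".

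The same section defines four classes by the share of the recurrent lesion inside the 95% isodose of the PTV: central (more than 95%), in-field (more than 80%), marginal (20% to 80%) and ex-field. The residual class is still a class of recurrences: "In all other cases, recurrences are defined as outside the radiation field". No class, denominator or time horizon is given for a patient without a recurrence.

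Other sections show that such patients are expected. PFS (section 6.1.2) runs "until the date of MRI evidence of tumor recurrence or death due to any cause", so death without MRI recurrence is a possible first event. For late toxicity, section 8.1.4 handles the same problem explicitly: "patients who died without experiencing late grade 3-5 side effects will be assessed as competing risk at the time of death".

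The propensity model (section 8.1.1) uses four baseline covariates: primary histology, GTV, KPS and age.

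**The concern.** As the classes are worded, a patient enters the logistic model only after a recurrence has been seen on MRI. Three consequences follow.

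1. The comparison conditions on an event that happens after treatment. Weights built on baseline covariates in the full arms need not balance the subset that recurs.
2. The share of ex-field lesions among recurrers moves when either hazard moves. Section 1.5 gives more effective cell kill in the enhancing area as the reason for the boost, so a selective change in local failure is the trial's own hypothesis. In that case the odds ratio cannot say whether local failure fell or distant failure rose.
3. A lesion with, say, 97% of its volume inside the isodose meets both the central and the in-field definition, so the outcome variable is not uniquely defined.

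What is at stake is the interpretation of a named secondary comparison. The primary endpoint and PFS are untouched.

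**Working it through.** **The plan's own figure.** The only related figure is the overall survival sample size (section 4.4): one-sided alpha 0.05, power 0.80, margin 1.4, true hazard ratio 0.90, 40/60 split. Events = (1.645 + 0.842)² / (0.4 × 0.6 × [ln(1.4/0.9)]²) ≈ 132. The plan anticipates that "the proportion of subjects observed with the event during the total study period is 0.8", and 132/0.8 = 165: "99 in the control group and 66 in the treatment group". This reproduces. No rate, sample size or power is stated for recurrence patterns.

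**Assumptions for the illustration (none from the protocol).** Constant cause-specific hazards; control median PFS 5 months; 20% of first events are deaths without MRI recurrence; 75% of control recurrences in-field (central included) and 25% ex-field; marginal left out for simplicity.

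- Total control hazard h = ln 2 / 5 = 0.1386 per month.
- Death without recurrence: 0.2h = 0.0277. In-field: 0.8 × 0.75h = 0.0832. Ex-field: 0.8 × 0.25h = 0.0277.

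**Formulas.** Among recurrers the odds of ex-field are h_ex / h_in. The odds ratio between arms is therefore HR_ex / HR_in, and the death hazard cancels. Cumulative incidence of cause k at 12 months is (h_k / h)(1 − exp(−12h)).

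| In-field HR | Ex-field HR | Ex-field share of recurrers | Odds ratio v control | 12-month in-field incidence | 12-month ex-field incidence |
|---|---|---|---|---|---|
| 1.0 (control) | 1.0 | 25.0% | 1.00 | 48.6% | 16.2% |
| 0.8 | 1.0 | 29.4% | 1.25 | 41.9% | 17.5% |
| 0.7 | 1.0 | 32.3% | 1.43 | 38.1% | 18.2% |
| 0.6 | 1.0 | 35.7% | 1.67 | 34.0% | 18.9% |
| 1.0 | 1.67 | 35.7% | 1.67 | 44.9% | 24.9% |

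The last two rows are the core of the point. A gain in local control and a rise in distant failure give the same odds ratio of 1.67.

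**Precision.** At an in-field HR of 0.6 and 12 months, expected counts are 99 × 0.162 = 16.1 and 99 × 0.486 = 48.1 in controls, and 66 × 0.189 = 12.5 and 66 × 0.340 = 22.4 in arm 1. Unweighted, SE(log OR) = √(1/16.1 + 1/48.1 + 1/12.5 + 1/22.4) ≈ 0.46, and ln 1.67 = 0.51 is about 1.1 standard errors.

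**Simulation under other assumed hazards.** Monthly hazards were in-field 0.09, ex-field 0.03 and death without recurrence 0.04, with 6,000 trials of 66 v 99 and 12 months' follow-up. With the ex-field hazard equal in both arms, the recurrers-only comparison is significant at two-sided 0.05 in 12% of trials at an in-field HR of 0.7, against 4% for a cause-specific comparison of ex-field recurrence. At an in-field HR of 0.5 the rates are 32% and 4.7%.

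**Does coding non-recurrers as no help?** No. Over in-field HRs of 0.7 and 0.5 and the hazards examined, the all-patient odds ratio for ex-field recurrence is still about 1.10 to 1.38 with an unchanged ex-field hazard. It also ignores censoring and unequal follow-up. With identical hazards in both arms (0.09, 0.03, 0.04; total 0.16), the ex-field proportion is (0.03/0.16)(1 − exp(−0.16 × 12)) = 16.0% at 12 months and (0.03/0.16)(1 − exp(−0.16 × 42)) = 18.7% at the 3.5 years that section 4.4 mentions.

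**The case against.** **The odds ratio is coherent.** Objective 5 asks about patterns on MRI, and where recurrences lie among patients who recur is a legitimate question. If in-field failure falls, the pattern really has shifted. This stands. A reader might infer that the planned result would be spurious or that the objective would be answered wrongly. The protocol does not support that, since it nowhere commits to reading a relative shift as an absolute rise in ex-field failure.

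**Deaths without recurrence do not drive the result.** A reader might also infer that early deaths hide a local gain. Under constant hazards the odds ratio does not depend on the death hazard, so this is not shown. Nor does the week-26 imaging entry in Table 3 bear on it: that is a data upload point, and MRI is taken in standard care, so deaths before it are not deaths without an MRI recurrence.

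**The restriction is inferred, and a final analysis plan is still to come.** True: section 8.1.2 names no population, and a denominator could be set later. But the method and the classes are already fixed, and neither natural denominator resolves the ambiguity.

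**The size is assumed.** Also true. The effects are modest against their standard error, and the 32% rejection rate needs a halved in-field hazard, beyond the 0.6 to 0.8 range tabulated.

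**The remedy has its own weaknesses.** Ex-field cumulative incidence also rises when in-field failure falls (16.2% to 18.9% above). Time-based methods depend on MRI timing, which is routine practice for the registry controls, and the share among recurrers is less exposed to this. Both stand as costs.

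**The overlap can be read in order.** The classes run from strictest to loosest, so a sensible reader would assign central first. The text does not say so, and the wording should be settled. It is a separate, smaller point.

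**Conclusion.** The point holds as a weakness of the chosen method. Section 8.1.2 in effect compares recurrers only. The resulting odds ratio is a valid relative measure, but it cannot separate fewer in-field failures from more ex-field failures, and the weights need not balance the patients it uses. With an unchanged ex-field hazard, assumed in-field hazard ratios of 0.8, 0.7 and 0.6 give odds ratios of 1.25, 1.43 and 1.67. These are illustrations under constant hazards, because the protocol gives no pattern-specific rates. The overlap of central and in-field is plain from the text.

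Severity is low to moderate: a non-key secondary objective is affected, and the plan already uses a suitable approach for late toxicity.

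**What to change.** Change section 8.1.2, or settle it in the final analysis plan that section 8.1 requires before formal analysis:

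- Analyse all patients. Compare arms with propensity-weighted cause-specific Cox models for each first-recurrence pattern.
- Report weighted cumulative incidence of each pattern, with death without MRI recurrence as a competing event, in line with section 8.1.4.
- Read the two together, because ex-field cumulative incidence rises somewhat when in-field failure falls even if the ex-field hazard does not change.
- Keep the distribution of patterns among recurrers as a descriptive table.
- Define in-field as more than 80% up to 95%, so that the classes are exclusive.

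The cost is mainly wording and a little more analysis, since PFS and OS already need the recurrence and death dates. Events per pattern will be few, and marginal and ex-field may need pooling. The results will depend on MRI timing in the registry controls, a limitation that PFS already shares.

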### **8.1.3 HRQoL in arm 1**

HRQoL will only be assessed in the experimental group. Reasons for missing baseline and follow-up questionnaires will be assessed. Linear Mixed Effects models will be used for regression analyses of HRQoL. In addition, the repeated measures of the EQ-5D-5L, QLQ-C15-PAL and BN20+2 functional and symptom scales will be assessed by time to deterioration (TTD) analyses. The time until definitive HRQoL score deterioration (TUDD) is defined as time from inclusion to a first deterioration of the score with a minimal clinically important difference (MCID) of at least 10 points as compared to the baseline score. With no further improvement of more than the MCID as compared to the baseline score or if the patient dropped out after deterioration, resulting in missing data. According to the construction of the HRQoL scores, deterioration corresponds to an increase (e.g., for symptomatic scales of the EORTC questionnaires and EQ-5D-5L) or a decrease (e.g., for functional scales) of the score.

Patients with no score available are excluded from the time-to-deterioration analyses.

Patients with no baseline score are usually censored at baseline and those with no follow up scores but with a baseline score are censored one day after baseline. Patients with no deterioration before drop-out from the study, including death, are censored at the time of last HRQoL questionnaire completion or last follow-up.

The TUDD estimation will be calculated using the Kaplan-Meier method and described using median and 95% CI.

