## 6. METHODS

### 6.1 Study parameters/endpoints

#### 6.1.1 Main study parameter/endpoint

The primary endpoint will be the time to death (overall survival (OS)) counted from the first date of ReRT until death due to any cause. Both treatments are finished within 2 to 3 weeks.

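### Time to definitive HRQoL deterioration censors death and is summarised by a Kaplan-Meier median, unlike late toxicity in the same arm; the direction of the error on the same data is clear, its size is not

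*Protocol*

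**What the plan says.** Section 8.1.3 defines TUDD for the EQ-5D-5L, QLQ-C15-PAL and BN20+2 scales, in addition to linear mixed models. Its rule for patients who never deteriorate is: "Patients with no deterioration before drop-out from the study, including death, are censored at the time of last HRQoL questionnaire completion" or, as an alternative date, at last follow-up. The estimator and summary are also fixed: "The TUDD estimation will be calculated using the Kaplan-Meier method and described using median and 95% CI".

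Section 8.1.4, for late toxicity in the same arm, uses cumulative incidence: "patients who died without experiencing late grade 3-5 side effects will be assessed as competing risk at the time of death".

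Section 4.4 gives the mortality planning figure: "Expected event rate at the minimal follow-up time of 12 months is 0.7 based on the literature". The event is death, because section 6.1.1 defines the primary endpoint as time "counted from the first date of ReRT until death due to any cause".

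Two features of the schedule matter for the size. Section 6.2 ends questionnaires at week 52 or at progression, whichever comes first. It also assigns EQ-5D-5L to the first 6 weeks and the EORTC forms to later time points. Table 3 schedules HRQoL at baseline without naming the form, and the Summary names only EQ-5D-5L there.

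**The concern.** A patient who has died cannot deteriorate afterwards, so death competes with deterioration. Censoring death treats that patient as someone who could still deteriorate at the rate seen in survivors. One minus Kaplan-Meier then describes a hypothetical cohort in which nobody dies, and only if death is unrelated to HRQoL decline. That is hard to accept in recurrent glioma, and the protocol declares no such target.

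The plan recognises the problem for late toxicity and gives no reason for treating TUDD differently. HRQoL is measured only in the experimental arm, so the absolute median is the result; there is no between-arm contrast in which the error could partly cancel. Section 1.2 presents HRQoL as information for patients' and physicians' decisions, so the median should describe something that can happen to these patients.

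**Working it through.** The protocol states no figure for TUDD, so there is none to reproduce. The check asks how far the planned estimator can lie from the cumulative incidence.

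**Inputs**
- Mortality at 12 months: 0.70 (section 4.4, a planning assumption). With a constant hazard, m = -ln(0.30)/12 = 0.1003 per month, which implies a median survival of ln 2/0.1003 = 6.9 months.
- Published median survival after re-irradiation: 7.7 to 11.5 months (section 1.1), that is m = 0.0900 to 0.0603 per month.
- Deterioration hazard d: not given. Assumed 0.05, 0.08 and 0.10 per month, constant.
- Rate of death before progression: not given. Assumed 0.01 to 0.03 per month.

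**Formulas at time t (months)**
- Kaplan-Meier with death censored: 1 - exp(-d t)
- Cumulative incidence: d/(d+m) × [1 - exp(-(d+m) t)]
- Highest cumulative incidence ever reached: d/(d+m)

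**Direction.** Each step of the cumulative incidence is the deterioration hazard multiplied by the proportion free of both deterioration and death. Each step of one minus Kaplan-Meier is the same hazard multiplied by the proportion free of deterioration only, which is at least as large. So on the same data one minus Kaplan-Meier is never the lower of the two.

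**Size at 12 months if every death fell under HRQoL observation (m = 0.1003)**

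| d | 1 - KM | Cumulative incidence | Ceiling |
|---|---|---|---|
| 0.05 | 45% | 28% | 33% |
| 0.08 | 62% | 39% | 44% |
| 0.10 | 70% | 45% | 50% |

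**Size at 12 months if only deaths before progression compete (d = 0.08, censoring at progression taken as non-informative)**
- m = 0.01: 0.08/0.09 × [1 - exp(-1.08)] = 0.889 × 0.660 = 59%
- m = 0.03: 0.08/0.11 × [1 - exp(-1.32)] = 0.727 × 0.733 = 53%
- Kaplan-Meier: 1 - exp(-0.96) = 62%

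The gap is then about 3 to 8 points.

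**Median (d = 0.08).** Kaplan-Meier gives ln 2/0.08 = 8.7 months. The cumulative incidence reaches 50% at -ln(1 - 0.5 × (d+m)/d)/(d+m):
- m = 0.01: 9.2 months
- m = 0.03: 10.6 months
- m = 0.1003: never, because the ceiling is 44%

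**Sensitivity to mortality.** With median survival 11.5 months (m = 0.0603) and d = 0.08, the cumulative incidence is 46% at 12 months and its ceiling is 0.08/0.1403 = 57%. A median then exists, but after month 12.

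**EQ-5D-5L to week 6.** With 70% one-year mortality, and deterioration hazards that would give 10% to 80% at one year without deaths, the gap at week 6 is 0.1 to 1.1 points.

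**The case against.** The strongest objection is that the simple model does not match the data this protocol collects. Questionnaires stop at progression, so a patient who progresses and later dies has already left HRQoL observation. Applying the full death hazard exaggerates the competition within the observed data. This stands, and it is why the 39% is an extreme and not the estimate.

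A reader might infer from the all-deaths table that Kaplan-Meier overstates deterioration by 17 to 25 points and reports a median for something that fewer than half ever experience. The documents do not support that as a general statement. It requires all deaths to occur under HRQoL observation and, for the 44% ceiling, the 6.9-month median survival implied by 70% mortality. At the longest survival quoted in section 1.1 the ceiling is 57%.

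A reader might also infer that the estimate must exceed the true probability of deterioration before death. That is not guaranteed. In a simulation on the protocol's visit weeks (deterioration hazard that would give 50% at one year without frailty or deaths, strong shared frailty, an assumed 4-month median to progression), one minus Kaplan-Meier was 24.0% against a true 23.9%, while the observed incidence was 11.7%. Such agreement comes from offsetting errors and does not justify the estimator. Only the comparison with cumulative incidence on the same data is certain.

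The instrument schedule also limits the size. The one-year figures apply to the EORTC scales only if they have a baseline score, which section 8.1.3 presumes and the schedule does not name. Without one, that section's own rule would censor those patients at baseline.

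Finally, the analysis is descriptive, sits beside mixed models and promises a median, not a 12-month percentage. Nor would the error flatter the 4-fraction schedule: overstated deterioration counts against it. These points bear on the weight of the finding, not on whether censoring death is appropriate.

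**Conclusion.** The point holds in a limited form. Section 8.1.3 fixes a rule that censors death where about 70% one-year mortality is expected, and it departs from section 8.1.4 without a reason. On the same data, one minus Kaplan-Meier is at least as high as the cumulative incidence, so the median is too early or may not exist as a real-world quantity.

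The size depends on three things the protocol does not settle: the deterioration rate, the share of deaths before progression, and whether the EORTC scales have a baseline score. Under constant hazards with an assumed 0.08 per month, the 12-month excess is about 3 to 8 points if only deaths before progression compete, and about 22 points (61.7% against 39.3%) as the extreme. For EQ-5D-5L to week 6 it is negligible. This should be corrected, but it concerns a secondary, single-arm, descriptive endpoint and leaves the overall survival conclusion untouched.

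**What to change.** In section 8.1.3:

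1. Estimate definitive deterioration by cumulative incidence (Aalen-Johansen), with death without prior deterioration as a competing event, in line with section 8.1.4.
2. State how progression is handled, because collection ends there. Either treat progression without prior deterioration as a further competing event, so that the result is deterioration before progression or death, or censor at progression and say that this assumes non-informative progression. The two answer different questions.
3. Report the composite of deterioration, progression or death, with its median, as the companion summary.
4. Choose one censoring date in place of the two alternatives now offered.

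The cost is analysis wording. Dates of death are already collected (section 6.2), progression is needed for PFS, and section 8.1 requires a final analysis plan before any formal analysis. No reanalysis can recover deterioration between progression and death, since no questionnaires are planned then; the report should say so. The form given at baseline should be named too, because TUDD on the EORTC scales depends on it.
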